## **Summary of the study protocol**

Project name: Computer-assisted non-fluent aphasia idiom Lang rehabilitation training

Objective: To explore the effect of idiom **training on** non-fluent aphasia, in order to find a new effective means of aphasia rehabilitation training to meet the rehabilitation needs of non-fluent aphasia patients.

Design type: a randomized controlled study

Study jects: Non-fluent aphasia patients after stroke

Sample size: Based on the method and purpose of this study, according to the results of formula  $n = \frac{2 \ln(1/\alpha) \ln(1/(1-\beta))}{(\ln(P_e) - \ln(P_c))^2}$ ,  $P_e$  and  $P_c$  are the positive rates of the test group and the control respectively (i. e., the proportion of patients with improved language function).

### **Entry standard**

#### **Inclusion criteria:**

- (1) Was diagnosed with aphasia through the aphasia Screening Form of China Rehabilitation Research Center, and was a non-fluent aphasia patient;
- (2) Primary school education or above;
- (3) Clear awareness and cooperation, normal intelligence before the onset, and no history of mental illness;
- (4) For non-fluent aphasia after ischemic stroke, the cerebral infarction site is the posterior inferior frontal gyrus of the superior side, and the disease is stable, and you can sit alone for more than 30min;
- (5) Informed and agreed to participate in this test, and sign the informed consent form;
- (6) Age is from 45 to 70 years old

#### **Exclusion criteria:**

- (1) Cognitive impairment;
- (2) Mental disorders;

- 
- (3) Binocular corrected visual acuity <1.0 or visual field defect;
  - (4) Hearing impairment;
  - (5) Ararthria;
  - (6) Complete aphasia, Wernicke aphasia, transcortex sensory aphasia and transcortex mixed aphasia;
  - (7) Misuse of speech;

**Baseline data**

Gender, age, education, type of stroke, area of disease, cerebral infarction, Aphasia Battery Of Chinese (ABC) score, Comprehensive activities of daily living (CADL) scale score

### **Observational indicators**

Aphasia Battery Of Chinese (ABC ) scale,all items score,  
including listening to understanding, oral expression, writing,reading four items; Comprehensive activities of daily living(CADL) scale score,, including 22 daily communication activities

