### **statistical analysis technique**

Two independent sample t-test, paired sample t-test

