Melodic Intonation Therapy (MIT) has gradually developed since the 1970s and is used today. It is a structured treatment procedure of aphasia by using melodic characteristics in language to promote

patient speech output. It is a structured procedure[13]. As the treatment of nonfluent aphasia, MIT is recognized by the few of many training methods[14]. And for such aphasia patients with good hearing comprehension but impaired speech expression, MIT is the most significantly effective in the treatment[15]. Using the specific melody, intonation, rhythm, stress, and left-hand percussion of the language material to improve the oral output of patients is the rehabilitation principle of MIT [16]. Idiom is a unique Chinese word collocation, although its melody is slightly weak, but it has the characteristics of songs do not have: ① idiom collocation fixed and neat, composed of 4 words, has a good sense of rhythm; ② has a certain story background, conducive to the extraction of patient words and oral expression, and idiom story background characteristics, make the training more interesting; ③ has a wide public familiarity[16,17]. Inspired by MIT, the present study used these characteristics of Chinese idioms to train idiom reading for non-fluent aphasia patients in order to improve their language function. Computer as the main tool of information, with its fast, convenient, image, and other characteristics, in the world popularization. At the same time, with the development of the "Internet + medical" mode, computer plays a huge role in the medical field. Its multimedia changes, such as graphics, audio and animation, provide strong technical support for the rehabilitation of aphasia patients. Therefore, computer is considered as a useful means of language rehabilitation[18]. Computer-aided language evaluation for aphasia

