### **3.5 Statistical analysis**

#### **3.5.1 Statistical Methods**

Statistical analysis was performed using the statistical software SPSS20.0, Data are represented in terms of ( $\bar{x} \pm s$ ), The study language function score and patient general data (age and disease duration) are the measurement data, Therefore, the t-test of two independent samples was used to compare between the experimental and

control groups, Two respective internal pre-posterior scores were compared using a paired sample t-test, Meverage of language function difference before and after the study using paired sample t-test; patient general data (including sex and stroke type) are count data, The chi-square test was used, Significance level =0.05.

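### The protocol names no primary outcome among four ABC domain scores and a CADL score, and the sample size rests on an outcome that is neither listed nor analysed

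*Protocol*

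**What the plan says.** Under Observational indicators, the protocol summary lists the ABC as "scale,all items score", and then gives its four domains together with the CADL score: "including listening to understanding, oral expression, writing,reading four items; Comprehensive activities of daily living(CADL) scale score,, including 22 daily communication activities". No score is ranked above another.

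Section 3.2 states a general aim about the rehabilitation effect of idiom training and names no scale.

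The summary gives the analysis as "Two independent sample t-test, paired sample t-test". Section 3.5.1 uses the independent-samples test between groups and paired tests within each group. It reserves chi-square for sex and stroke type and closes with "Significance level =0.05". It states no order of testing and does not say whether the between-arm or the within-arm result decides.

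The sample-size text, in the summary and again in the sample-size section, uses positive rates in the two arms, meaning the proportion of patients with better language function after the study. What counts as improvement is not defined. This proportion appears neither among the indicators nor in Section 3.5.1.

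**The concern.** A 0.05 level describes the trial's conclusion only if the result that carries the conclusion is fixed in advance. Here several scores have equal standing, and the proportion used for sizing cannot serve as an implied primary because no analysis of it is planned. The deciding outcome could therefore be picked once the results are known. The error rate of the claim that training works would then exceed the stated level, by an amount that depends on how many scores are in play and how strongly they correlate. That cannot be repaired after unblinded results have been seen.

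**Working it through.** **Inputs**
- Level per test: 0.05 (Section 3.5.1). Sidedness is not stated; two-sided is assumed.
- Scores: four ABC domains and one CADL scale score, so k = 5 (Observational indicators). Section 3.5.1 refers only to the language function score, so testing of CADL is inferred from the indicator list and the summary's analysis line. k = 4 is therefore shown as well.
- Time points: baseline and one assessment at 2 weeks (Research methods and steps), so repeated visits add no multiplicity.
- Correlation ρ between test statistics: not given. Assumed equal for all pairs, with 0 to 0.9 shown.

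**Reference case**

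The 0.05 is a chosen input, so there is no derived figure to reproduce. With one deciding test, 1 − 0.95¹ = 0.05, as stated.

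**Independent tests (ρ = 0)**
- Five scores: 1 − 0.95⁵ = 0.226.
- Four ABC domains: 1 − 0.95⁴ = 0.185.
- Upper bounds whatever the correlation: 5 × 0.05 = 0.25 and 4 × 0.05 = 0.20.

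**Correlated tests**

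With equicorrelated normal statistics, the chance of at least one false positive is

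1 − ∫ φ(u) [Φ((1.96 − √ρ·u)/√(1−ρ)) − Φ((−1.96 − √ρ·u)/√(1−ρ))]ᵏ du,

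evaluated numerically.

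| ρ | k = 5 | multiple of 0.05 | k = 4 | multiple of 0.05 |
|---|---|---|---|---|
| 0 | 22.6% | 4.5 | 18.5% | 3.7 |
| 0.3 | 20.9% | 4.2 | 17.4% | 3.5 |
| 0.5 | 18.3% | 3.7 | 15.6% | 3.1 |
| 0.7 | 14.8% | 3.0 | 13.0% | 2.6 |
| 0.8 | 12.7% | 2.5 | 11.4% | 2.3 |
| 0.9 | 10.2% | 2.0 | 9.4% | 1.9 |

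**False positives in favour of training only**

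The nominal rate is 2.5%. For five independent scores, 1 − 0.975⁵ = 11.9%; at ρ = 0.9 the rate is 5.1%. For four scores the corresponding figures are 1 − 0.975⁴ = 9.6% and 4.7%. The absolute rates are about half the two-sided ones, and the relative inflation is much the same.

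**After the fix**

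One named primary outcome tested at 0.05 returns the error of the main claim to 0.05.

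**The case against.** **An SAP may exist.** Section 3.4 refers to a statistical plan that is not shown. This stands for the adjustment procedure: its absence from the protocol is no fault. It does not cover the choice of primary outcome, which belongs in the protocol, and it does not explain why the sample-size outcome matches no indicator and no test in the same document.

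**The protocol never says that any one significant score is enough.** This stands. A reader might infer an any-of-five success rule, but no such rule is written. What can be said is that no rule is given, so the error rates above are conditional on that reading.

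**The 22 CADL activities.** A reader might count each activity as a test and reach 4 + 22 = 26. The documents do not support that. The wording describes the content of one scale score, and the baseline and data-collection text also list a single CADL score. No item-level testing is planned.

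**Fewer tests, and not independent ones.** Testing of CADL is only inferred, and domains of one language battery measured in the same patients are unlikely to be independent. Both points are fair. They bring the two-sided rate to about 9% at four scores and ρ = 0.9, which is still nearly twice the stated level.

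**The aim is worded as exploratory.** The same sentence goes on to seek a new effective means of training, which is an efficacy conclusion.

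**Conclusion.** The point holds as a missing primary outcome. The protocol gives equal rank to four ABC domain scores and a CADL score, tests at a single 0.05, and sizes the trial on a proportion that it neither lists nor analyses.

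The size is conditional. If any one significant score were read as benefit, the two-sided false-positive chance would be 10–23% for five scores or 9–19% for four, over assumed correlations from 0.9 to 0. For claims favouring training it would be about 5–12% or 5–10%, against 2.5%. At low to moderate correlation this is three to four and a half times the stated level; at 0.9 it is about double. Confidence is high that no primary outcome is named, and lower on the number of tests, which the text leaves unclear.

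**What to change.** Before any between-arm results are seen:

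1. Name one primary outcome, compared between arms at 2 weeks at two-sided 0.05. ABC oral expression is a reasonable candidate: Section 3.1 describes the story background of idioms as "conducive to the extraction of patient words and oral expression". An ABC total is also defensible, because the same section gives the overall aim as better language function. Choosing in advance matters more than which of the two is chosen.
2. Label the remaining ABC domains and the CADL total as secondary. They can be supportive only, or tested with a multiplicity adjustment if the primary succeeds; the procedure can sit in the SAP.
3. State that the between-arm comparison decides, not the within-arm paired tests.
4. Bring the sample-size basis, in both the summary and the sample-size section, into line with the chosen primary.

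**Cost:** a few sentences in Observational indicators and Section 3.5.1, a rework of the sample-size text in two places, and a lesser claim status for the secondary scores.

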### **statistical analysis technique**

Two independent sample t-test, paired sample t-test

## **3. Text of the study protocol**

### **3.1 Research background and project approval basis**

Aphasia is an acquired language disorder with impairment or loss of communication ability after brain damage (generally in the left brain), that is, impaired ability to understand and form language symbols, and impaired decoding and coding of language componentsAt least 1 / 3 of the patients developed aphasia after stroke. Its main clinical characteristics are: oral English disorders, listening and comprehension disorders, retelling disorders, naming disorders, reading (reading and comprehension) disorders and writing disorders.According to the main clinical characteristics of aphasia, aphasia is divided into: Broca (Motor) aphasia, Wernicke (comprehension) aphasia, conductive aphasia, transcortical motor aphasia, transcortical sensory aphasia, transcortical mixed aphasia, complete aphasia, and named aphasia. According to the patient's oral English, aphasia is divided into fluent aphasia and non-fluent aphasia. The common clinical manifestation of non-fluent aphasia is unusually rare, often less than 50 words per minute, or even less than 10 words per minute. Hard speech is another feature; fluency aphasia is characterized by more speech, hard speech, normal pronunciation and intonation, but

---

less information. Although aphasia is defined as a language disorder, emotional and psychosocial changes often accompany aphasia. Aphasia is reported to be an important factor in emotional depression, social isolation and low quality of life after stroke. Language communication with others is the first step in forming social interpersonal relations, Most clinical experts believe that effective communication is an indispensable part of ensuring the quality of life of patients with aphasia. aphasia significantly affects the quality of life of patients, so language rehabilitation care for aphasia should be highly valued by clinical rehabilitation nursing staff.

There are many rehabilitation training methods of aphasia at home and abroad, including for example, (1)Schuell stimulation therapy, refers to the damage of language symbol system application controlled, strong auditory stimulation, to promote the patients' language function reconstruction and communication ability recovery, is the basis of a variety of aphasia treatment, is one of the most widely used language therapy. (2) uses compulsory induced language therapy (C ILT), which uses forced verbal communication and suppresses non-oral communication, and performs a lot of targeted language training. With the traditional

The advantage of CIL T over language therapy is that it can improve language function in a short period of time and successfully apply the improved function to daily life; (3) transcranial magnetic stimulation (TMS) is performed by placing a "figure 8" insulated copper coil on the scalp, using the magnetic field to form a current in discrete brain areas, creating a rapidly fluctuating magnetic field through the skull, to achieve the recovery of language function; (4) needle stimulation refers to the method of Chinese classical acupoint acupuncture. Traditional Chinese medicine meridian theory believes that different acupoints have their special effects. Modern medicine shows that different acupoints have different special brain activation areas through functional imaging tests, and these brain activation areas may be corresponding to the curative effect of acupuncture; (5) Melodic intonation therapy (MIT), using the melodic characteristics such as tone, rhythm, stress, rhythm, to promote the recovery of patients' speech functionclass. At present, the rehabilitation treatment of language disorders in stroke aphasia patients is complex and diverse. However, due to the different types, severity, gender, nationality, culture, age, hobby, etc. of aphasia patients, the needs for effective rehabilitation care measures for aphasia are also different. Therefore, in order to meet the rehabilitation needs of different aphasia patients and maximize the improvement of language rehabilitation nursing effect, rehabilitation nursing staff need to constantly seek more new effective means of aphasia rehabilitation training.

Melodic Intonation Therapy (MIT) has gradually developed since the 1970s and is used today. It is a structured treatment procedure of aphasia by using melodic characteristics in language to promote

patient speech output. It is a structured procedure[13]. As the treatment of nonfluent aphasia, MIT is recognized by the few of many training methods[14]. And for such aphasia patients with good hearing comprehension but impaired speech expression, MIT is the most significantly effective in the treatment[15]. Using the specific melody, intonation, rhythm, stress, and left-hand percussion of the language material to improve the oral output of patients is the rehabilitation principle of MIT [16]. Idiom is a unique Chinese word collocation, although its melody is slightly weak, but it has the characteristics of songs do not have: ① idiom collocation fixed and neat, composed of 4 words, has a good sense of rhythm; ② has a certain story background, conducive to the extraction of patient words and oral expression, and idiom story background characteristics, make the training more interesting; ③ has a wide public familiarity[16,17]. Inspired by MIT, the present study used these characteristics of Chinese idioms to train idiom reading for non-fluent aphasia patients in order to improve their language function. Computer as the main tool of information, with its fast, convenient, image, and other characteristics, in the world popularization. At the same time, with the development of the "Internet + medical" mode, computer plays a huge role in the medical field. Its multimedia changes, such as graphics, audio and animation, provide strong technical support for the rehabilitation of aphasia patients. Therefore, computer is considered as a useful means of language rehabilitation[18]. Computer-aided language evaluation for aphasia

Evaluation and computer-assisted aphasia rehabilitation treatment are two main aspects of computer application in aphasia rehabilitation care. Computer-assisted language assessment for aphasia refers to the conversion of a paper version of the aphasia assessment scale pictures and text on a computer and later presented by screen and speech, thus in the language assessment for patients with aphasia. Computer-assisted language function evaluation software for aphasia at home and abroad mainly includes: language disorder instrument ZM 2.1, Computer speech assessment and rehabilitation system TG PX 111 And the Parrot series for aphasia therapy class. Computer-assisted aphasia rehabilitation care mainly consists of three main forms: The first is to restore impaired language function through semantic, phonetic, or grammar characteristics, namely obstacle-oriented therapy; the second is to realize patients' daily life communication activities and train patients to use the residual language as effectively as possible; and the third is a participatory therapy by using computers to encourage more participation in social communication, in which most current aphasia rehabilitation computer software tend to be disorder-oriented therapy. Domestic common aphasia rehabilitation nursing computer software has language disorder instrument ZM2.1, Accessible computer language system U 1 And the computer speech evaluation and rehabilitation system TG PX 111 etc.; foreign computer software in computer script training Aphasia Scripts™, IMITATE computer-assisted aphasia treatment system And the Parrot series of aphasia treatment software class. According to Katz, the application of computers in aphasia rehabilitation is mainly divided

---

into two main categories: computer-assisted therapy (CAT) and computer-independent therapy (COT)。

### **3.2 Study Purpose**

Main purpose: To explore the rehabilitation effect of idiom **training** on non-fluent aphasia, in order to seek a new effective means of aphasia rehabilitation training to meet the rehabilitation needs of non-fluent aphasia patients.

### **3.3 Study design**

This study is a randomized controlled study. No randomized or any study protocol-driven treatment will be administered or offered to the subjects during the course of the study. If clinically applicable, the treating physician should make the treatment decision and make the choice of treatment options.

### **.3.13 Subjects**

The subject population in this study was patients with non-fluent aphasia after stroke.

Selection criteria:

- (1) Was diagnosed with aphasia through the aphasia Screening Form of China Rehabilitation Research Center, and was a non-fluent aphasia patient;
- (2) Primary school education or above;
- (3) Clear awareness and cooperation, normal intelligence before the onset, and no history of mental illness;
- (4) It is non-fluent aphasia after ischemic stroke, and the cerebral infarction site is the posterior inferior frontal gyrus of the dominant side, and the disease

---

In the stable period, you can adhere to sit alone for more than 30min;

(5) Informed and agreed to participate in this test, and sign the informed consent form;

(6) Age is from 45 to 70 years old

Exclusion criteria: (means the object that does not meet the study requirements even if they meet the inclusion criteria)

(1) Cognitive impairment;

(2) Mental disorders;

(3) Binocular corrected visual acuity <1.0 or visual field defect;

(4) Hearing impairment;

(5) Disarthria; loss of speech;

(6) Complete aphasia, Wernicke aphasia, transcortex sensory aphasia and transcortex mixed aphasia;

### **.23.3 Determine of sample size for study**

Based on the method and purpose of this study, the pre-test was conducted, and the sample size was calculated using formula  $n = (+) 2 / [2 (\sin^{-1} e - \sin^{-1} c)^2]$ .  $P_e$  and  $P_c$  were the positive rates of the test group and the control, respectively (i. e., the proportion of patients with improved language function).

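### The trial is sized on the proportion of patients who improve, but the listed analysis compares mean language scores by t-test, so the sample size does not belong to the planned comparison.

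*Protocol*

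**What the plan says.** **Sizing.** The synopsis introduces its formula with "Based on the method and purpose of this study, according to the results of formula" and explains that Pe and Pc "are the positive rates of the test group and the control respectively (i. e., the proportion of patients with improved language function"). The body, in the section on determining the sample size (printed as .23.3), says that a pre-test was conducted and defines the same two quantities as the "positive rates of the test group and the control, respectively (i. e., the proportion of patients with improved language function"). As printed, the synopsis formula uses logarithms, n = 2 ln(1/α) ln(1/(1−β)) / (ln Pe − ln Pc)². The body formula uses inverse sines, and some of its symbols were lost when the PDF was read.

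**Analysis.** The synopsis lists "Two independent sample t-test, paired sample t-test" and nothing else. Section 3.5.1 states: "The study language function score and patient general data (age and disease duration) are the measurement data". It continues: "Therefore, the t-test of two independent samples was used to compare between the experimental and" control groups, with paired t-tests within each group. The only test for categorical data is for baseline description: "patient general data (including sex and stroke type) are count data, The chi-square test was used". The significance level is 0.05, with sidedness not stated.

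**Outcomes.** The observational indicators are the Aphasia Battery of Chinese (ABC), with four item scores, and the communication scale (CADL). No cut-off on either scale is given to define an improved patient.

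**The concern.** A sample size is meaningful only for a particular outcome and a particular test. Here the inputs are two response rates, while the between-group evidence will be a difference in mean scores. The detectable difference for a t-test depends on the SD of the score, and a pair of response rates does not supply that without further assumptions about the cut-off and the distribution. A reader cannot tell what difference in ABC score the trial is able to detect, and a null t-test result could not be interpreted against the planned power.

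The two printed formulas add a second, lesser problem. They are different in kind, and the synopsis version behaves oddly if β has its usual meaning.

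**Working it through.** **1. Is there a planned figure to reproduce?** No. The text shown contains no sample size, Pe, Pc, power or dropout rate. Every rate, SD ratio and power below is an assumption, at two-sided α = 0.05.

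**2. Sizing against analysis.** This needs no formula.

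| Place in the protocol | Outcome type | Test |
|---|---|---|
| Synopsis, sample size | Binary (improved or not) | Two proportions |
| Body, sample size (.23.3) | Binary (improved or not) | Two proportions |
| Synopsis, statistical technique | – | t-tests only |
| Section 3.5.1, language score | Continuous | Independent and paired t-tests |
| Section 3.5.1, chi-square | Sex, stroke type | Not a response rate |

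No row in the analysis tests the proportion on which the trial is sized.

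**3. Size of the gap.** At 80% power, (1.960 + 0.842)² = 7.849.

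- Two proportions, arcsine form, 0.80 vs 0.50: 7.849 / [2(1.1071 − 0.7854)²] = 37.9, so 38 per arm.
- Two means, difference of 0.5 SD: 2 × 7.849 / 0.25 = 62.8, so 63 per arm.
- Two means, difference of 0.8 SD: 2 × 7.849 / 0.64 = 24.5, so 25 per arm.

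The last two are normal approximations; an exact t calculation adds about one per arm.

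**4. Direction of the error.** Suppose that an improved patient is one above a cut-off on a normally distributed change score with equal variance in both arms.

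- Rates of 0.80 and 0.50 then imply a difference of 0.842 − 0 = 0.842 SD of the change. A t-test on change needs 2 × 7.849 / 0.842² = 22.2, so about 23 per arm, against 38 by arcsine.
- For 0.90 and 0.60 the difference is 1.282 − 0.253 = 1.028 SD, giving about 15 per arm against 29.8.
- For a t-test on the post-treatment score instead, with equal SD before and after and correlation ρ between the two, the SD of the change is √(2(1−ρ)) times the score SD. The requirement becomes 22.2 / [2(1−ρ)]. It equals 37.9 when 2(1−ρ) = 0.585, that is ρ ≈ 0.71. Above that correlation the stated approach would undersize the trial; below it, it would oversize it.

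The direction therefore turns on which score is tested and on ρ, and the document settles neither.

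**5. The two printed formulas.** Rates 0.80 and 0.50; ln 20 = 2.996, ln 1.6 = 0.470.

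| Reading | 80% power | 90% power |
|---|---|---|
| Synopsis, β = type II error | 2 × 2.996 × 0.223 / 0.470² = 6.05 | 2.86 |
| Synopsis, β = power | 43.7 | 62.5 |
| Arcsine with square roots | 37.9 | 50.7 |

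With β as the type II error, ln(1/(1−β)) falls from 0.223 to 0.105, so n at 90% power is 0.47 times n at 80%, whatever the rates. With β as power, n rises. The document does not define β.

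**The case against.** The best defence concerns the formulas. The body formula visibly lost symbols in reading, and the synopsis formula stands in a nearly identical sentence with the same Pe and Pc and a squared difference of transformed rates in the denominator. It may be a misreading of one and the same arcsine formula. That would not be an error in the plan. This stands: the formula discrepancy can be raised only as something to check.

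A reader might infer from the synopsis formula that the trial is several times too small. The documents do not support that. Nothing shows that the synopsis formula was applied; the meaning of β is open; and no sample size is stated. A figure of about six per arm, or a power computed from it, would describe a trial that nobody planned.

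A reader might equally infer from the mismatch that the trial is underpowered. That is unproven too: on the assumptions in step 4, sizing on the dichotomy is conservative for a t-test on change.

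Finally, the data-management section refers to a statistical plan that is not shown, and a test of the proportion might appear there. That limits the wording to what the protocol lists. It does not remove the conflict, because the protocol itself states both a sizing basis and an analysis, and the two disagree.

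**Conclusion.** The mismatch holds. It rests on plain prose in the synopsis, the sample-size section and section 3.5.1, and does not depend on how any formula was extracted. The stated sizing, and any power attached to it, belongs to a comparison of proportions that is not among the tests the protocol lists. It should be corrected, since the between-group score comparison carries the trial's main purpose and no sizing in the document relates to it.

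No error in patient numbers can be stated. The illustrations (38 per arm for proportions; 63 or 25 for means) show only that the answers are not interchangeable. They rest on assumed rates, SD ratios, two-sided α and 80% power. The difference between the printed formulas is a matter for checking against the source PDF. If the synopsis really reads ln(1/(1−β)) with β as the type II error, that formula is wrong, because n falls as power rises.

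**What to change.** Put one identical calculation in the synopsis and in the sample-size part of section 3.3, for the outcome and test actually used.

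- Name the score on which the trial is sized. For an independent t-test on the 2-week ABC score: n per arm = 2(z(1−α/2) + z(1−β))² SD² / δ², with β defined as the type II error.
- For a t-test on change scores, use the same formula with the SD of the change.
- Apply the factor (1−ρ²) only if section 3.5.1 is also changed to a baseline-adjusted analysis (ANCOVA). It does not fit the t-tests now listed.
- Take the SD from the pre-test if ABC scores were recorded there. The protocol does not say that they were; if not, state the SD as an assumption with a range.
- State α with its sidedness, power, δ, SD and the resulting n.
- Check both printed formulas against the source PDF, and delete the synopsis formula if it reads as described above.

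If the enrolment number is already fixed, keep it and restate the detectable difference or power that it gives. The cost is a short recalculation and a restated figure that may look less favourable. No extra patients are needed.
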